### Secondary Efficacy Measures

The secondary efficacy parameters for the study include the following measures:

The self-reported number of relapses, which is assessed through a single item asking participants to complete the number of relapses they had the last 7 days. Data are collected from participants at the fourth session (*t*
_1_), 3 days after *t*
_1_ (*t*
_2_), weekly from *t*
_1_ through week 4 (*t*
_3_-*t*
_6_), and at weeks 12 (*t*
_7_) and 24 (*t*
_8_) after *t*
_1_.The self-reported number of cravings, which is assessed through a single item asking participants to complete the number of cravings they experienced in the last 7 days. Data are collected from participants at the fourth session (*t*
_1_), 3 days after *t*
_1_ (*t*
_2_), weekly from *t*
_1_ through week 4 (*t*
_3_-*t*
_6_), and at weeks 12 (*t*
_7_) and 24 (*t*
_8_) after *t*
_1_.Self-efficacy on being aware of experienced cravings, which is assessed with the single item: “How well are you aware of your cigarette cravings?” Answers are given on a 10-point scale from 1 (very poorly) to 10 (very well). Data are collected from participants before the quit day (-*t*
_2_), at *t*
_1_, *t*
_2_, weekly from quit day at *t*
_3_-*t*
_6_, and at weeks *t*
_7_ and *t*
_8_.Self-efficacy on managing cravings, which is assessed with the single item: “How well do you manage your cravings?” Answers are given on a 10-point scale from 1 (very poorly) to 10 (very well). Data are collected from participants at -*t*
_2_, *t*
_1_, *t*
_2_, weekly at *t*
_3_-*t*
_6_, and at weeks *t*
_7_ and *t*
_8_.Power of control in managing cravings is assessed with 6 items. An example item is “If I am in a situation where I celebrate with my friends...,” then, the answer for the experimental group is “It will be more difficult to use Ph.o.S. app to control my craving for tobacco,” and for the comparator group is “It will be more difficult to do something to control my craving for tobacco.” Answers are given on a 7-point scale from 1 (totally agree) to 7 (totally disagree). The other items present similar tempting situations like when participants are stressed or angry. Data are collected from participants before the quit day at -t_2_ and -t_1_ and after *t*
_1_ at weeks t_2_, t_6_, t_7_, and t_8_.

### Additional Measures

Additional measures of mainly psychological variables will be collected in order to use them as possible explanatory variables of the primary or secondary efficacy measures. Moreover, usability, fidelity, and data extracted from the phone database will be collected for validation purposes.

Physical activity behavior. Self-reported data regarding participants’ current physical activity behavior as recorded with the International Physical Ativity Questionaire (IPAQ) [53] will be collected at -*t*
_2_ and -*t*
_1_ and at weeks *t*
_7_ and *t*
_8_. Self-reported physical activity behavior through self-reports, before the quit day at -*t*
_2_ and -*t*
_1_, will be verified by measuring their step counts (via pedometer Omron HJ-152) the last week before measurement day. IPAQ records the physical activity of 4 intensity levels for the last 7 days: (1) vigorous-intensity activities such as aerobics, (2) moderate-intensity activities such as leisure cycling, (3) walking, and (4) sitting.Relapse situation efficacy as recorded with the Relapse Situation Efficacy Questionnaire (RSEQ) [54] will be assessed before the quit day at -*t*
_2_ and -*t*
_1_. RSEQ consists of 75 simple items assessing participants’ confidence in their ability to resist the temptation to smoke in a wide variety of contexts. A 4-point response scale is used from 1(not at all confident) to 4 (extremely confident).Attitude toward, intention to, and perceived behavioral control of increasing physical activity behavior will be measured through a self-reported questionnaire before and after quit day at -*t*
_2_ and *t*
_1_. Similarly, attitude toward, intention to, and perceived behavioral control of quitting smoking will be measured before quit day at -*t*
_2_. Likewise, attitude toward, intention to, and perceived behavioral control of craving management will be measured during the fourth session at *t*
_1_. Attitude toward all 3 behaviors (ie, increasing physical activity, quitting smoking, and managing cravings) is assessed with 6 items using a 7-point semantic differential scale (ranging from -3 to +3): ‘‘To (behavior) in the following month will for me be...’’: good-bad, unpleasant-pleasant, wise-silly, easy-difficult, healthy-unhealthy, important-not important. Similarly, intention is measured with 3 items: “In the following month...”: (1) “I intend to (behavior),” (2) “I will try to (behavior),” (3) “I plan to (behavior).” Answers are given on a 7-point scale ranging from 1 (very likely) to 7 (very unlikely). Correspondingly, perceived behavioral control is measured with 4 items, for example: “For me to (behavior) in the next month is...,” and rated on a 7-point scale, with participants answering from 1 (easy) to 7 (difficult).Usability of the Ph.o.S app for the experimental group only will be collected through the System Usability Scale (SUS) self-reported questionnaire [55] 1 week (*t*
_3_) and 1 month (*t*
_6_) after participants have started using it. SUS is a 10-item scale giving a global view of subjective assessments of usability. Answers are given on a 5-point scale from 1 (strongly agree) to 5 (strongly disagree). Moreover, a follow-up qualitative assessment when the user stops using the app is performed in order to determine the reasons for discontinuation and possible other means they use to manage cravings effectively.All participants are asked fidelity check questions during the follow-up measure at *t*
_2_, *t*
_3_, *t*
_6_, *t*
_7_, and *t*
_8_. Questions are related to additional help (eg, pharmacological, mHealth apps) used to manage cigarette cravings. Additional questions for the experimental group are related to the ways they use the Ph.o.S app.Information from the Ph.o.S app is also collected constantly during the follow-up period for the experimental group from the time they start using it (*t*
_2_-*t*
_8_). Data, such as frequency of use and frequency of successful and unsuccessful efforts to manage craving through the suggested solutions, will be extracted and used to verify the corresponding self-reported questions. Additional data will be extracted for descriptive purposes.

### Data Collection Procedure

Screening data at time point -*t*
_3_ will be collected via an online questionnaire to determine eligibility for all participants who respond via the various recruitment strategies. The questionnaire consists of a short overview of the aim of the study and questions regarding the person’s addictions, quitting history, willingness to quit, general health, and readiness for physical activity. The website used to assess eligible participants is a safe and secure site called Fluid Surveys. People who are eligible, based on the online assessment, receive a follow-up telephone call from the study nurse to verify eligibility and will be invited to come to the health center to complete the consent to participate and the baseline measures.

Baseline data and behavioral and psychological self-reported data at time points -*t*
_2_, -*t*
_1_, and *t*
_1_ will be collected during the first, third, and fourth sessions of the smoking cessation intervention in a paper-and-pencil format, administered by the study nurse in a quiet area of the unit. Follow-up data at all follow-up time points (*t*
_2_-*t*
_8_) will be collected via online questionnaires after an invitation from the research assistant to participants, via email or SMS, to complete the questionnaires. In addition, data from the phone app users (experimental group only) will be collected during the follow-up period. Users’ phone data will be uploaded daily to a secure university server reserved for this purpose.

Once participants have participated in the final meeting, the researchers will make every reasonable effort to follow the participant for the entire follow-up period of 6 months. Participants may, however, withdraw from the study for any reason at any time. However, early discontinuation of Ph.o.S app for any reason is not a reason for exclusion from the study.

### Data Management

The University of Jyväskylä is responsible for storing and protecting the research data. The research registry is kept at the University of Jyväskylä in a locked cabinet. All electronic data will be stored on a university computer with password protection. Only the principal investigator and the research assistant will have access to the computer-based data. All participants will be assigned a code number in order to protect their confidentiality. All stored data will be under the unique code number. All data will be entered electronically. Original study forms will be entered and kept on file at the participating site. Participant files are stored in numerical order and in a secure and accessible place and manner. Participant files will be stored for a period of 3 years after completion of the study.

### Statistical Methods

Generalized linear mixed models will be used to examine differences between the groups on the dichotomous primary outcome variable: abstinent versus smoker status at the 6-month follow-up time point (ie, *t*
_8_). The differences at all follow-up time points will also be examined, but the 6-month follow-up is considered to be the primary focus. Descriptive statistics will be used to report process data. Any covariates identified in the preliminary analyses will be added to the model. Linear mixed models will be used to analyze the secondary efficacy measures for data that are normally distributed or are approximate to a normal distribution (via data transformations). For count variables, a generalized Poisson mixed model will be applied. Alternatively, we will use nonparametric tests by time point separately.

Finally, 3 separate logistic regressions on the primary dichotomous outcome (abstinent-smoker) will be performed using the theory of planned behavior (TPB) constructs of quit smoking behavior and increased physical activity behavior at the -*t*
_2_ time point and the TPB constructs of manage cravings behavior at the *t*
_1_ time point as predictors. Linear regressions for the continuous variables of the secondary efficacy outcomes will be used to test the predictive ability of all TPB constructs. All analyses will be conducted using intent-to-treat principles with participants remaining in their originally assigned groups after randomization regardless of adherence or protocol deviation. This is done to increase the likelihood that group differences are due to the intervention and unaffected by biases that lead to an overestimation of the intervention effect [56].

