Mobile technologies are a means for providing individual-level support to health care users and a promising platform for health interventions [22]. Behavioral intervention technologies offer promising opportunities to expand psychological practice [23]. Several mobile health interventions have been designed to increase healthy behavior (eg, to promote smoking cessation or increase activity levels) and are also cost effective [24]. A review of mobile phone-based interventions for smoking cessation revealed only 4 trials: 2 using SMS text messages and 2 using the Internet and mobile phones. The trials were heterogeneous. However, when the data from both programs were pooled, they found statistically significant increases in both short- and long-term self-reported quitting [25]. A more recent systematic review [26] concluded that SMS-based smoking cessation interventions more than doubled biochemically verified smoking cessation at 6 months. Moreover, the self-help methods have been indicated in previous literature as effective for long-term effects [4] and the use of mobile phone applications as a self-help method sounds promising.

Therefore, a mobile phone application has been developed for the needs of this study. The aim of the app is to support quitters in managing their cigarette cravings and abstaining over the long term by using exercise as the main behavioral substitution strategy. The mHealth app called “Physical over Smoking (Ph.o.S)” includes a data collection mechanism to collect real-time data regarding relapses. The Ph.o.S app was developed based on evidence-based practices for relapse prevention after smoking cessation. Following that, a trial has been designed to test the effectiveness of the mHealth app.

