### Trial Design

This study is a 2-armed randomized clinical trial. Participants identified as eligible and who give their consent to participate will receive a smoking cessation program consisting of 3 group sessions (once per week). After the quit day, participants will be randomly assigned to 2 groups. Both groups will have a separate fourth session where they will receive training on relapse prevention and a plan to cope with cravings. The intervention group will receive an additional short training session on how to use the Ph.o.S app as an additional support tool whenever they experience cravings in their everyday life during the follow-up period. Preintervention, postintervention, and 6-month follow-up assessments will be conducted. Table 1 displays an overview of the study’s timeline and the schedule of enrollment, interventions, and assessments. Multimedia Appendix 1 displays the detailed measurement time points for each group.

**Table 1 table1:** Study timeline: overview of schedule of enrollment, interventions, and assessments.

Timeline points	Schedule				
	Screening for eligibility	Intervention: quit smoking (3 sessions)	Quit day: allocation	Intervention: manage cravings (4th session)	Follow-up assessment
-*t* _3_	X				
-*t* _2_		X			
-*t* _1_		X			
*t* _0_			X		
*t* _1_				X	
*t* _2_ (3 days after)					X
*t* _3_ (1 weeks after)					X
*t* _4_ (2 weeks after)					X
*t* _5_ (3 weeks after)					X
*t* _6_ (4 weeks after)					X
*t* _7_ (12 weeks after)					X
*t* _8_ (24 weeks after)					X

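### The covariate rule for the primary model is data-driven and not limited to variables measured before allocation, so a likely mediator such as later physical activity could be adjusted for and part of the app's effect removed

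*Protocol article*

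**What the plan says.** Statistical Methods in the protocol article describes a generalized linear mixed model for abstinent v smoker status at t8, the 24-week point. It then gives this rule for the same model: "Any covariates identified in the preliminary analyses will be added to the model". The article says nothing on which variables are candidates, by what criterion they are chosen, or at what time they must have been measured.

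Additional Measures says that mainly psychological variables are collected to "use them as possible explanatory variables of the primary or secondary efficacy measures". The first of them is physical activity, which "as recorded with the International Physical Ativity Questionaire (IPAQ) [53] will be collected at" -t2 and -t1 (sessions 1 and 3) and again at t7 and t8 (weeks 12 and 24).

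On timing, Trial Design says: "After the quit day, participants will be randomly assigned to 2 groups". Table 1 puts allocation at t0, before the fourth session at t1. On mechanism, the Introduction describes the app as "using exercise as the main behavioral substitution strategy".

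Statistical Methods also commits all analyses to intention to treat, so that group differences are more likely to be due to the intervention.

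**The concern.** A covariate measured before allocation cannot be affected by the app, so adjusting for it leaves the question unchanged. A covariate measured afterwards can be affected. If it lies on the path from app to abstinence, adjusting for it changes the question from the effect of the app to the effect that does not pass through that covariate.

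Physical activity at weeks 12 and 24 is the clearest case. If the app works as designed, activity is related both to arm and to abstinence, and a search for predictors of abstinence would tend to find it. This does not depend on who makes the choice or on whether that person is blinded. It also works against the stated reason for the intention-to-treat commitment.

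The trial is small. With no effect, about 0.25 × 50 = 12.5 participants would be abstinent. At the article's detectable difference the number is 0.25 × 25 + 0.59 × 25 = 21. With so few, one added covariate can change the conclusion.

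**Working it through.** **Inputs from the article (Power).** 25 per arm, 25% abstinent in the comparator group, 59% in the experimental group, two-sided 0.05.

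**The plan's own figure.** The article states power above 0.80 for 25% v 59%. With the pooled-variance formula:

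power = Φ[(Δ√n − z√(2p̄q̄)) / √(p₁q₁ + p₂q₂)]

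Here Δ = 0.34, n = 25, p̄ = 0.42, √(2p̄q̄) = 0.698 and √(p₁q₁ + p₂q₂) = 0.655.

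- Two-sided, z = 1.960: Φ[(1.700 − 1.368)/0.655] = 0.694. The unpooled form gives 0.737.
- One-sided, z = 1.645: Φ[(1.700 − 1.148)/0.655] = 0.800.

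So 59% reproduces only with a one-sided test. That is a separate matter. The baseline used below is the simulated two-sided power, about 0.74.

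**Step 1: the cost of adjusting for a mediator.** The documents give no mediator strength, so the strengths are assumed and a range is shown. Covariate M is normal with SD 1 and mean s × arm. The outcome model is logit P(abstinent) = a + d·arm + b·M. The values of a and d are solved so that marginal abstinence is 25% and 59%. The test is a likelihood-ratio test for arm, with 2000 simulated trials per case (Monte Carlo error at most √(0.25/2000) = 0.011). The path through M adds s × b to the log odds and d is the remainder, so the share carried by M is sb/(sb + d).

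| s (SD) | b per SD | s × b | d | share via M | power unadjusted | power adjusted for M |
|---|---|---|---|---|---|---|
| 0.5 | 0.8 | 0.40 | 1.26 | 0.24 | 0.745 | 0.518 |
| 0.8 | 0.8 | 0.64 | 1.02 | 0.39 | 0.730 | 0.356 |
| 0.8 | 1.2 | 0.96 | 0.90 | 0.52 | 0.736 | 0.248 |

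A repeat with fresh random numbers gave 0.53, 0.34 and 0.26 adjusted. With stronger mediators (b = 1.0 to 2.0), power fell from 72-74% to 26-35% when M carried half the effect, and to 5-7% when it carried all of it.

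**Step 2: would a screen pick M?** In the same three cases, M was added only if its association with abstinence had p < 0.10. It was picked in 89-99% of trials, and power was 0.54, 0.35 and 0.26. The loss therefore does not come from forcing M into the model.

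**Step 3: type I error.** No true effect, candidates unrelated to the outcome, 25 per arm.

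| Covariate choice | 10 or 20 candidates, 600 runs each, 25% or 42% abstinent | 5, 10 or 15 candidates, 2000 runs each, 25% abstinent |
|---|---|---|
| None | 0.047-0.065 | 0.048-0.063 |
| Those with p < 0.10 against outcome | 0.043-0.070 | 0.060-0.064 |
| Model with smallest treatment p value | 0.098-0.128 | 0.091-0.106 |

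Monte Carlo error is about √(0.05 × 0.95/600) = 0.009 in the first column and 0.005 in the second. Choosing on outcome association barely moves the error rate. Only a choice guided by the treatment result roughly doubles it.

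**Step 4: the alternative.** In the stronger-mediator setting (b = 1.0 to 2.0), a prognostic covariate not affected by the app raised power from about 74-75% to 78-89%. Adjustment as such is not the problem.

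**The case against.** The strongest reply is that Statistical Methods defines no candidate pool. Linking its rule to Additional Measures is the reader's inference. The theory-of-planned-behavior constructs have their own regressions in Statistical Methods, and a condensed article may leave the covariate list to an analysis plan. Much of this stands. The missing list is not the point; the point is the rule that the article does state, which admits any covariate found in the data and sets no time limit.

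The reply also narrows the set of convincing examples:

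- **Additional help during follow-up.** The item reads: "Questions are related to additional help (eg, pharmacological, mHealth apps) used to manage cigarette cravings". It is a fidelity check, and Additional Measures assigns fidelity, usability and phone data to validation. It is not good evidence of a candidate covariate.
- **Craving-management constructs at t1.** These are measured in the fourth session itself, after allocation but before real-life app use, so they are weak examples of a mediator.
- **Physical activity at t7 and t8.** This remains, and it is enough.

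A reader might also infer that the rule deprives the p value of its stated meaning. The documents do not support that. They describe adding covariates to one model, not choosing among models by their treatment result, and the error rates of 0.09-0.13 belong only to the latter.

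Finally, the power figures rest on assumed strengths. They show what adjusting for such a mediator would do, not what the trial will show.

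**Conclusion.** The concern holds in a limited form. The article commits the primary comparison to covariates found in preliminary analyses and does not restrict them to measures taken before allocation. Physical activity at weeks 12 and 24 is collected as a possible explanatory variable of the primary outcome and is a likely mediator. If it entered the model, power would fall from about 0.74 to about 0.25-0.54, assuming a shift of 0.5-0.8 SD and a log odds ratio of 0.8-1.2 per SD. That it is in the pool is inferred from Additional Measures and the absence of any restriction. The main harm is a hidden true effect. False positives become materially more likely only if the choice is guided by the treatment result, which the article does not say. The sentence should be changed.

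**What to change.** Replace the covariate sentence in Statistical Methods with:

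> The primary model contains arm (with time and arm-by-time terms where repeated measures are modelled) and a small covariate set fixed before outcome data are examined, limited to variables measured before allocation (-t3 to -t1), for example the Tobacco Dependence Screener score. No variable measured after allocation is used as an adjustment covariate in a treatment comparison. Covariates suggested by preliminary analyses appear only in an additional model labelled exploratory, shown beside the primary and unadjusted results.

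The screener score is only an example. Eligibility Criteria shows that it is already collected from everyone at screening as a continuous score. Physical activity at -t2 or -t1 would also qualify.

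The cost is a change of wording, with no new data. The downside is that a chance imbalance in another baseline variable is handled only in the exploratory model. Trial Status has follow-up running to the end of December 2015, so on the article's timetable the set can be fixed before the 24-week data are complete.

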### Trial Aim

The aim of this study is to present the protocol of a study that assesses the effectiveness of the Ph.o.S app, which helps abstaining users to manage their cigarette cravings. The study will examine the quit rates of abstaining users of the app versus the quit rates of a comparator group for a 6-month period after quitting smoking. The trial’s main hypothesis is that users of the Ph.o.S app will have higher 7-day point prevalence abstinence rates during the follow-up measures in comparison to the comparator group (trial registration number ISRCTN55259451).

Four additional hypotheses have been proposed:

Users of the Ph.o.S app will have fewer self-reported relapses during the follow-up measures than the comparator group will.Users of the Ph.o.S app will report higher self-efficacy from being aware of experiencing cravings than the comparator group will.Users of the Ph.o.S app will report higher self-efficacy in managing cravings in relapse situations than the comparator group will.Users of the Ph.o.S app will report a higher power of control to manage cravings in everyday situations than the comparator group will.

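### The fallback of separate nonparametric tests at each time point leaves the pre-allocation score and the repeated measures of the two self-efficacy items unused, and names no single test for either hypothesis.

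*Protocol article*

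**What the plan says.** Two of the four additional hypotheses in the Trial Aim section concern self-efficacy: one on being aware of cravings, one on managing them. The second reads: "Users of the Ph.o.S app will report higher self-efficacy in managing cravings in relapse situations than the comparator group will". Neither names a time point.

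Under Secondary Efficacy Measures, each is a single item scored 1 to 10. For the awareness item the schedule begins: "Data are collected from participants before the quit day", at -t2, and the managing item is also collected at -t2. Both are then collected at t1 and at t2 to t8. The Data Collection Procedure places -t2 at the first session. Under Trial Design, "After the quit day, participants will be randomly assigned to 2 groups", so -t2 precedes allocation. Table 1 puts t1 (the fourth session) after allocation at t0.

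The Statistical Methods section gives the first-line analysis: "Linear mixed models will be used to analyze the secondary efficacy measures for data that are normally distributed or are approximate to a normal distribution", with data transformation allowed. Count variables get a Poisson mixed model. The remaining route is: "Alternatively, we will use nonparametric tests by time point separately". A sentence on covariates, "Any covariates identified in the preliminary analyses will be added to the model", sits with the primary outcome and does not name the baseline score. The statement that 6 months is the main focus is also made for the dichotomous primary outcome.

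**The concern.** A single bounded 1 to 10 item, answered by people who have just stopped smoking, may well be skewed or pile up at the top of the scale. The items are not counts, so if transformation fails, the by-time-point tests become the main analysis of these two hypotheses.

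A plain two-group test at one wave ignores the person's other waves and leaves out anyone missing at that wave. The rule that dropouts count as smokers supplies no self-efficacy score. Such a test also contains no -t2 value, although that score is already collected and cannot have been affected by allocation. In a trial of 50 people that itself lists sample size as a limitation, this is precision available at no cost.

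Separately, each hypothesis would be examined at seven follow-up waves with none named in advance. A true difference at 6 months is then more easily missed, and one isolated significant wave can be read as support.

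**Working it through.** **Inputs from the protocol article.** 50 participants, 25 per arm (Power). Seven follow-up waves, t2 to t8 (Table 1). Two-sided 0.05, stated for the primary outcome and assumed here for each secondary test.

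**Inputs that are assumptions.** The article gives no effect size, standard deviation or within-person correlation for these items, and no power or error rate to reproduce. Assumed here: a standardised difference d, a correlation ρ between the -t2 score and a later score, and a correlation r between follow-up waves.

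**Step 1: precision at one time point.** Noncentral t power with noncentrality d × √(25/2) / √(1 − ρ²). Degrees of freedom are 48 without the covariate and 47 with it. For d = 0.7, d × √12.5 = 2.475.

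| Analysis | √(1 − ρ²) | Noncentrality | Power |
|---|---|---|---|
| Unadjusted | 1 | 2.475 | 68% |
| -t2 covariate, ρ = 0.2 | 0.980 | 2.526 | 70% |
| ρ = 0.3 | 0.954 | 2.594 | 72% |
| ρ = 0.4 | 0.917 | 2.700 | 75% |
| ρ = 0.5 | 0.866 | 2.858 | 80% |

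The gain runs from about 2 to 12 percentage points and passes 5 points only from about ρ = 0.4. With a smaller assumed effect, d = 0.5, a normal approximation gives 42% unadjusted, and 46%, 53% and 70% at ρ = 0.3, 0.5 and 0.7. The direction is the same.

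These are t-based figures. A simulation of a 1 to 10 item with a ceiling (d = 0.7, r = 0.5) compared a rank test at t8 with a baseline-adjusted analysis at t8. Power was 61% for the rank test against 62%, 64% and 71% at ρ = 0.2, 0.3 and 0.5.

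**Step 2: chance of at least one false positive over seven tests.** If the waves were independent, it is 1 − 0.95⁷ = 30.2%. For correlated waves, seven two-sided z tests with equal correlation r were simulated (400,000 runs):

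| r | At least one p < 0.05 |
|---|---|
| 0 | 30% |
| 0.3 | 27% |
| 0.5 | 23% |
| 0.7 | 18% |
| 0.9 | 11% |

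Mann-Whitney tests on a rounded 1 to 10 scale with 25 per arm gave 23.2% at r = 0.5, so the z-test figures carry over. If t1 is also tested, eight tests give about 34% (r = 0) down to 12% (r = 0.9). With one time point named in advance, the figure is about 5%.

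**Step 3: are the two effects linked?** No. A baseline-adjusted test at each of the seven waves would inflate the error in a similar way. A single unadjusted rank test at t8 would hold it at about 5%.

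**The case against.** The strongest defence is that this is a conditional fallback. The first-line mixed model does use the repeated measures, and whether non-normality will trigger the fallback is conjecture. Baseline covariates, the exact rank test and the named contrast are often left to an analysis plan, which is not shown. That holds for details merely absent. It does not cover the fallback itself, which the article states: testing by time point separately.

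Several stronger readings are tempting and are not supported:

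- A reader might infer that the fallback has a 23% false-positive rate. That figure needs a between-wave correlation of 0.5, which no document gives. Only the range can be stated.
- A reader might infer that discarding the baseline causes the inflation. It does not (Step 3).
- A reader might infer that the plan moves from one test to seven. The article names no single contrast for the mixed model either, so the one-test benchmark is not the plan's own.
- A reader might infer a very large power loss by comparing a rank test at t8 with an adjusted average over t2 to t8. That average is a different contrast and gains mainly by assuming a constant effect. On the same t8 contrast the gain is small to moderate.
- A reader might infer that the -t2 value is ruled out. The wording does not literally exclude a nonparametric method that uses it, such as rank analysis of covariance; it simply includes none.

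It also stands that -t2 is taken while people still smoke, about six months before t8. A weak correlation, and hence little gain, is quite possible.

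**Conclusion.** The point holds in a limited form. As worded, the fallback uses neither the repeated measures nor the pre-allocation score of the two self-efficacy items.

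The cost in precision at one time point is 2 to 12 points of power, assuming d = 0.7 and a baseline correlation of 0.2 to 0.5; it is small if that correlation is weak. Independently, seven unadjusted tests with no named time point put the chance of a false positive at about 11% to 30% per item, for assumed between-wave correlations of 0.9 to 0. Even the low end is twice the nominal 5%. If the 6-month focus were extended to these hypotheses, the inflation would largely disappear, but the text states that focus only for the primary outcome.

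Severity is low to moderate: the outcomes are secondary, the analysis is conditional, and the primary comparison is unaffected.

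**What to change.** In Statistical Methods, replace the fallback for the two self-efficacy items, before any group comparison is made:

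1. Fit one mixed model to t2 to t8 with group, time, group by time, and the -t2 score of the same item as covariate. Do not use t1 as the baseline, because it follows allocation.
2. Name one group contrast per item as the test of its hypothesis, preferably t8, to match the focus of the primary outcome.
3. If residuals are not normal, keep this model and obtain the p value by permuting participants' group labels, or bootstrap the interval.
4. Report by-wave rank tests as descriptive only.

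The cost is a few sentences, one degree of freedom and slightly more analysis work. No new data or visits are needed. The gain from item 1 may be small if the pre-quit score predicts later scores poorly; item 2 removes the multiplicity within each item either way.
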